## Abstract

**Background:**

The screening of digital footprint for clinical purposes relies on the capacity of wearable technologies to collect data and extract relevant information’s for patient management. Artificial intelligence (AI) techniques allow processing of real-time observational information and continuously learning from data to build understanding. We designed a system able to get clinical sense from digital footprints based on the smartphone’s native sensors and advanced machine learning and signal processing techniques in order to identify suicide risk.

**Method/design:**

The Smartcrisis study is a cross-national comparative study. The study goal is to determine the relationship between suicide risk and changes in sleep quality and disturbed appetite. Outpatients from the Hospital Fundación Jiménez Díaz Psychiatry Department (Madrid, Spain) and the University Hospital of Nimes (France) will be proposed to participate to the study. Two smartphone applications and a wearable armband will be used to capture the data. In the intervention group, a smartphone application (MEmind) will allow for the ecological momentary assessment (EMA) data capture related with sleep, appetite and suicide ideations.

**Discussion:**

Some concerns regarding data security might be raised. Our system complies with the highest level of security regarding patients’ data. Several important ethical considerations related to EMA method must also be considered. EMA methods entails a non-negligible time commitment on behalf of the participants. EMA rely on daily, or sometimes more frequent, Smartphone notifications. Furthermore, recording participants’ daily experiences in a continuous manner is an integral part of EMA. This approach may be significantly more than asking a participant to complete a retrospective questionnaire but also more accurate in terms of symptoms monitoring. Overall, we believe that Smartcrises could participate to a paradigm shift from the traditional identification of risks factors to personalized prevention strategies tailored to characteristics for each patient.

**Trial registration number:**

NCT03720730. Retrospectively registered.

## Background

### Suicide risk and monitoring

Over 800,000 people die because of suicide every year worldwide. For each suicide, there may have been more than 20 other attempted suicides. A previous attempt is the major predictor of death by suicide [1]. However, many other outcomes associated with suicidal behaviors should be considered in order to strength preventative strategies prevention. Environmental, Clinical, and genetic [2] risk factors have been intensively studied among suicide attempters in order to improve personalization and effectiveness of preventative programs [3]. Suicide risk assessment relies on standard follow-up outpatient visits in a psychiatric clinic. This assessment includes a mental status examination, a brief update on the history of the patient’s present illness (including a safety assessment of risk of self-harm, suicide). In order to develop a form of assessment that can more accurately track patients’ symptoms and risks between visits, we conducted several studies aiming to add ecological momentary assessment to traditional follow up strategies [4] [5]. Advances in sensors technology, and artificial intelligence methods (AI) also draw new perspectives for behavior ecological assessment [6]. Sleep disturbances and food intakes are not one of suicide risk factors usually screened in routine suicide risk monitoring [7].Yet this clinical information could play a central role in suicide risk identification and prediction.

### Sleep, eating disorders and suicide risk

Sleep loss and sleep disturbances are associated with an increased risk of suicidal behavior, including suicidal ideation, suicide attempt, and completed suicide [8]. This relationship is consistent across psychiatric diagnoses and age groups [9]. The increased risk of suicidal ideation and suicide attempts among patients with early or late awakening times was demonstrated in representative samples of Korean [10] and British [11] adolescents of both genders. Chui et al. observed in a pooled sample of adolescents a linear dose–response relationship between sleep duration and suicide plans [12]. Rossler et al. showed that the correlates between sleep disorders including short sleep duration and suicidality was also observed in adults [13]. In a 30-year longitudinal cohort study of adults people, authors showed that the more severe the sleep problems are, the more pronounced is suicidality, including suicide ideation and behaviours. Interestingly these patterns persist even if we control for socio-demographics and in particular for accompanying mood, anxiety, or substance-use disorders, [14]. Changes in appetite are closely connected with depressive symptomatology and suicidal behavior [15]. Appetite has already been used in the prediction of suicidal risk [16]. Regarding eating disorders, negative self-image variables have been associated with suicide attempt history in anorexia and suicide attempts completions in women with bulimia [17]. In fact, in a cohort study of eating disordered subjects, the risk for suicide attempt was 4.70 (95% CI 1.41–15.74) in patients with eating disorders compared to matched (age, sex, place of residence) general population controls and further increased to 11.30 (95% CI 6.90–18.50) in those patients with history of previous suicide attempt [18]. A recent study found that suicide attempters had lower body mass index (BMI) and waist circumference, as well as decreased levels of serum [19].

### Suicide risk management in the e-health era

The integration of smartphones and wearables into medical practice has heralded the electronic-health (e-health) era. E-health involves the integration of new technologies into routine clinical practice by increasing networking possibilities between patients and clinicians. Recent trials using mobile electronic devices have proven successful in real-world and real-time monitoring and have improved the assessment possibilities in a large panel of clinical settings [20]. The assessment of the patient’s dynamic relationships between events and disease course is enhanced by the development of momentary data collection strategies, such as experience sampling methods (ESM) and ecological momentary assessment (EMA) [21]. These approaches, which rely on delivering informative contents and self-administered questionnaires, reduce the recall bias as they are done in real time [22]. Electronic devices are also able to perform passive (or autonomous) data gathering, i.e., to extract information about the users without any effort on their part. Actigraphy, geolocation, and communication activity are usual features of current smartphones and may be indicators of the patient’s behavior if they are properly processed. Overall, an extensive panel of physical and mental conditions can be remotely monitored [23]. Smartphones can embody such sensors and provide EMA features relying on patient self-reports. Finally, the data digital footprints, which is the automatically accumulated by-products of technological devices, offer a promising opportunity for research and clinical decision making [24].

The collected data can be processed and transferred over the Internet to a remote clinical back-end server for further analysis, assessment, decision making and intervention. AI is a set of analysis methods which permits to extract relevant information from any dataset. AI uses data mining techniques to get sense for the data. a set of techniques that can be used to explore treatment and outcome questions in large clinical databases and help develop algorithms and guidelines for problems where controlled data are difficult to obtain. The data mining process includes several steps, including data capture, data selection, data processing, and machine learning. Abdullah et al. reported that combining self-reported data with data from several smartphone sensors and communication patterns resulted in reliable prediction of the Social Rhythm Metric, a clinically-validated marker of stability and rhythmicity for individuals with bipolar disorder [25] Voice features from phone calls can also be collected and analyzed during everyday life in naturalistic settings. For inferring rhythmicity, a key marker of wellbeing for individuals with bipolar disorder. Another platform proposed A method to predict schizophrenia based on anomaly detection was developed using Beiwe, a platform able to perform data mining on smartphone data [26]. EMA has been successfully used for real-time self-reporting of symptoms and behavior—for example, Husky et al. showed the utility and feasibility of using EMAs to study suicidal ideations [27].

Taking into account the strengths and pitfalls of existing suicide risk assessment methods, we have designed a system capable to combine EMA and continuous monitoring of patients using the smartphone’s and/or wearable’s sensors and data entry in order to monitor and predict suicide risk. Both poor sleep quality and disturbed appetite are clinical markers of depression, with a bidirectional relationship. Their changes could precede the increase of suicidal behavior as sleep and appetite are both influenced by mood state and regulated by the serotonergic system. Our hypothesis is that tracking sleep and appetite regularly through self-report could serve as a consistent and non-biased shortcut to assess mood state, its biological underpinnings and could potentially predict suicidal behavior.

### Objectives

The overall study goal is to determine the relationship between wish to die, and suicide attempt and changes in sleep quality and disturbed appetite using Smartphone and wearable technology based using ecological momentary assessment (EMA).

The principal objective of the study is to identify the correlation between quality of sleep monitored via the digital footprint and suicidal events including and suicide attempts in a cohort of suicidal patients.

Secondary objectives are:
Establish the extent to which change in appetite is related to and suicide attempts.Clarify the timeline of the relationship between sleep disturbances and suicidal behavior.Determine the emotional impact of the use of the app during suicide related outcomes assessed.Develop personalized algorithms based on the EMA protocol and motor activity markers to assess the risk of suicide attempts.

## Method and design

### Study design and setting

This study is a pragmatic, prospective, multisite controlled trial with two parallel groups. The study setting is outpatient clinics and emergency departments at four clinical centers across two countries (Jimenez Diaz Foundation, Spain, University Hospital of Nimes, France).

### Participants

To be eligible for the study, patients must be 18 years or older, attend an outpatient clinic or emergency departments of participating clinical services and owning an android or IOS smartphone. Exclusion criteria are being less than 18 years old, refusal to participate to the study, and patients and in emergency situations where their state of health does not allow obtaining written consent. Patients who are unable or unwilling to provide informed and signed consent will be also excluded.

This study was built on the results of previous studies we conduced exploring the preferences of patient regarding eHealth based suicide assessment [28, 29]. Patients were involved in the design of this study in a preliminary step of the application conception which assed the feasibility and the burden of such approach in a sample of outpatients [30]. Patient were informed they could have access to the final result of the study during a routine medical visit, according to the ethic committee query.

### Intervention and control

After agreeing to participate, clinician will collect a signed consent for each patient. Patient will be assigned to intervention or control group weather they have a personal history of suicide attempt or not. Patient with a current suicidal behavior disorder (according to DSM-5), i.e. having attempted suicide in the current year, will be assigned to the intervention group.

Patient with no history of suicide behavior will be assigned to the control group. Both intervention and control group will receive as usual follow up. monitoring visits. In the intervention group, each participant will be assessed with an EMA protocol using two smart phones apps. The first app will ask questions following a dynamic protocol (quality and duration of sleep, wish to live and wish to die, and questions regarding emotional status), the second app will record diurnal activity that is related with sleep quality using smartphone sensors. Additionally, a subsample of participants of the intervention group will be monitored with a wearable armband to assess sleep phases and physiological changes during sleep and EMA assessment. Control group will only receive as usual follow up procedure and monitoring procedure of the study protocol (see Fig. 1).

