### Primary outcome

The primary outcomes are suicidal events assessed by Columbia-Suicide Severity Rating Scale (C-SSRS) in control and intervention group during the 6-month follow-up period.

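### Groups are defined by suicide-attempt history, so comparing suicidal events between them reflects prior risk, and the sleep analysis that fits the principal objective is not made primary

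*Protocol article*

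**What the plan says.** All references are to the protocol article.

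- **Study design and setting** describes a "pragmatic, prospective, multisite controlled trial with two parallel groups".
- **Intervention and control** sets the groups by history: "Patient will be assigned to intervention or control group weather they have a personal history of suicide attempt or not". Patients with a current suicidal behaviour disorder, defined as "having attempted suicide in the current year, will be assigned to the intervention group". For controls: "Patient with no history of suicide behavior will be assigned to the control group".
- The same section gives digital monitoring to one group only: "In the intervention group, each participant will be assessed with an EMA protocol using two smart phones apps". Controls have usual follow-up and the study's monitoring procedures.
- **Primary outcome**: "The primary outcomes are suicidal events assessed by Columbia-Suicide Severity Rating Scale (C-SSRS) in control and intervention group during the 6-month follow-up period".
- **Objectives** words the principal aim as follows: "identify the correlation between quality of sleep monitored via the digital footprint and suicidal events including and suicide attempts in a cohort of suicidal patients".
- **Suicide risk and monitoring** (Background): "A previous attempt is the major predictor of death by suicide".
- **Sample size** plans 1000 patients, 500 per site, and expects 100 re-attempts. It then describes the sample as 1000 attempters and claims 80% power, two-sided at 0.05, for changes in suicidal outcomes related to sleep and appetite.
- **Data analysis** plans descriptive summaries by site and treatment, adjustment for covariates on which groups differ significantly, multi-level logit models with sleep and appetite among the predictors, and hazards models for time to re-attempt.

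**The concern.** A study labelled as a controlled trial, with arms called intervention and control and a primary outcome collected in both, invites a comparison of that outcome between arms. Here the variable that decides the arm is the one the protocol itself names as the major predictor of death by suicide. A raw difference in suicidal events would mostly restate who was put in which group. It could be mistaken for an effect of the apps, in either direction.

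There is also a mismatch of question and population. The principal objective is an association within suicidal patients, between sleep measured digitally and suicidal events. The control group has neither the condition nor the measurement. The article does not say which analysis of which patients answers the principal objective, and the power statement describes a sample in which the control group does not exist.

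**Working it through.** **1. Overlap of exposure and history.** Set side by side, the rules in Intervention and control give:

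| Attempt history | Group | Apps |
|---|---|---|
| Attempt in the current year | Intervention | Yes |
| No suicidal behaviour ever | Control | No |
| Only attempt before the current year | Covered by the general sentence on personal history, but by neither specific sentence | Not clear |

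No patient without a history is given the apps, and no patient with one is assigned to control. Within any level of attempt history there is nothing to compare. Adding covariates, as Data analysis proposes, cannot repair this, because the variable that needs adjusting is the group variable itself.

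**2. Who can inform the principal objective.** It needs digitally monitored sleep and a suicidal population. The intervention group has both and the control group has neither. The logit and hazards models in Data analysis contain sleep and could be fitted in the intervention group. The section neither calls one of them primary nor limits it to that group.

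**3. The stated power.** The 80% cannot be reproduced, because the article refers to pilot effect sizes and standard deviations without printing them. The detectable effect can be back-solved. For one continuous predictor in a patient-level logistic model:

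ln(OR per SD) = (z₀.₉₇₅ + z₀.₈₀) / √(N·p·(1−p)), with z₀.₉₇₅ + z₀.₈₀ = 1.960 + 0.842 = 2.802.

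- As stated, N = 1000 and p = 100/1000 = 0.10: 2.802/√90 = 0.295, so OR = 1.34.
- If 500 are attempters and all 100 re-attempts occur among them, p = 0.20: 2.802/√80 = 0.313, so OR = 1.37.
- If 500 are attempters and the 10% rate holds (50 events): 2.802/√45 = 0.418, so OR = 1.52.

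For a hazards model with 100 events, ln(HR per SD) = 2.802/√100 = 0.280, so HR = 1.32. The 500 attempters are an assumption. The article gives 500 per site and no number per group.

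**4. Illustration of the confounding.** Suppose 500 patients per group and no effect of the apps at all. Take 10% events in attempters (100/1000) and assume a control rate. The probability that a two-sided 5% test of two proportions is significant is then:

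| Assumed control rate | Risk ratio | Odds ratio | P(significant) |
|---|---|---|---|
| 0.5% | 20 | 22.1 | 1.00 |
| 1% | 10 | 11.0 | 1.00 |
| 2% | 5 | 5.4 | 0.9997 |
| 5% | 2 | 2.1 | 0.85 |

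If all 100 re-attempts fell among 500 attempters, their rate would be 100/500 = 20%, and the probability is 1.00 in every row. If the apps halved attempters' risk from 10% to 5% against 1% in controls, the test would still be significant, with the app group looking worse, with probability 0.96.

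**The case against.** The strongest reply is that the protocol never plans the comparison. The Primary outcome section says in whom events are assessed; it does not say that the groups are tested against each other. No objective concerns whether the apps prevent suicidal events. The sample size concerns sleep and appetite, the regression models name no group term, and the Discussion sets the study apart from randomised controlled trials. This largely stands. A reader might infer that the trial plans a control-versus-intervention test and would go on to report harm from the apps. The documents do not support that, because no such test is written. What remains is that the design label, the arm names, the summaries by treatment and the adjustment for group differences all point to a comparison, and nothing disclaims one.

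A reader might also infer that no analysis serves the principal objective. That goes too far: the logit and hazards models relate sleep to suicidal outcomes. What is missing is the link from one of them to the primary outcome and to the attempter cohort.

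Thirdly, a reader might call the assignment sentences contradictory. They are better described as ambiguous. The current-year sentence does not say that only such patients enter the intervention group, so the general sentence could place earlier attempters there. The patient-flow figure, which might settle this, is not available here.

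Finally, the event-rate illustration mixes assumptions. The 10% comes from a sample described as 1000 attempters, it counts re-attempts although C-SSRS suicidal events may be broader, and both the control rates and the equal split are assumed. That is correct, and the figures carry no more weight than an illustration.

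**Conclusion.** The point holds as a fault of design description and alignment. Attempt history and app exposure coincide, so a comparison of suicidal events between the groups cannot say anything about the apps, and the planned adjustment cannot change that. This follows from the assignment rule alone and needs no assumed figure. Controls cannot contribute to the principal objective. The models that could answer it are planned but not designated primary or confined to the attempter cohort.

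The sample-size text adds a real inconsistency: 1000 recruited patients cannot all be attempters if some are controls. Its size depends on the unstated split. With 500 attempters, the detectable OR per SD moves from about 1.34 to 1.37 (100 events) or 1.52 (50 events), ignoring clustering and other covariates. The risk ratios and rejection probabilities above rest on assumed control rates and an assumed 500/500 split. They are not properties of any test in the protocol.

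**What to change.** 1. **Study design and setting; Primary outcome.** Describe a prospective cohort of attempters with a descriptive comparison group. Report control event rates descriptively and state that no inference about the apps will be drawn from them.
2. **Data analysis.** Designate as primary the model relating sleep to suicidal events over 6 months in the monitored attempter cohort.
3. **Sample size.** Say whether controls count toward the 1000. If they do, give the number of attempters and the expected events among them, and restate the power or the detectable effect.
4. **Intervention and control.** Reconcile the sentence on personal history with the one on the current year, so that patients whose only attempt was earlier have one stated group.

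The cost is mainly wording and needs no new data collection. The controlled-trial label and any between-group claim are given up. If controls are part of the 1000, the stated precision for the sleep association becomes less favourable.

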**Fig. 1 Fig1:**
[figure not shown]
Patient flow in intervention group and control group

### Primary outcome

The primary outcomes are suicidal events assessed by Columbia-Suicide Severity Rating Scale (C-SSRS) in control and intervention group during the 6-month follow-up period.

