#### Outcomes measures

We will use complementary strategies to obtain the primary outcome measures and assess adverse events. Assessments will be carried out by trained clinicians (Psychologist, Psychiatrist or Psychiatrist Residents up to second year) at outpatient clinics and emergency departments.

Researchers will check the hospital attendance data especially the emergency records.

The assessment of suicidal behaviors will include at the inclusion and completion of follow-up:
The Columbia Suicide Severity Rating Scale a scale that showed good sensitivity and specificity to identify the most at risk subjects [35].If a suicide attempt has occurred, the suicide intent scale [36] and the Risk Rescue Rating Scale.

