#### Suicide and sleep monitoring

Evaluation of the principal objective will be monitored via in-person interviews (see baseline assessment subsection) and EMA self-questionnaires including wish to live, wish to die, suicidal ideation, and suicide attempt during the follow-up period. The Suicidal Status Form [37] the Perceived Social Support Questionnaire (PSSQ,) and the Interpersonal Needs Questionnaire [38] have been incorporated into pop-ups to our EMA app to increase the participation rate during inactive periods [31].

The MEmind App will provide questions following a dynamic smartphone based assessment protocol exploring quality of sleep. The EB2 app will record diurnal activity that is related with sleep quality using smartphone sensors. EB2 will be validated with polysomnographic registers (see Fig. 2). EB2 is designed to collect information about the users’ physical and physiological activity level. This application has been developed for the Android mobile platform and works in combination with the arm Band. SmartPhone and the arm Band communicate via Bluetooth 4.0. This application obtains information from the user by accessing the built-in sensors in the host Android SmartPhone and the arm Band. Through the process of data logging the Sensor Logger APP records both the information from the SmartPhone and arm Band. This double recording of information by the Sensor Logger APP allows it to obtain enough information from inertial sensors to determine the user’s activity level during the recording process [39]. The heart rate signal and Galvanic skin response are also recorded to determine the emotional state of the user. In our study participants in the Smartcrisis group will be monitored with a wearable armband to assess sleep phases and physiological changes during sleep.

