### Sample size

We propose to recruit 1000 patients from two sites and expect a total of 100 suicide re-attempts during the follow-up period. We plan to recruit 500 patients per site (total of 1000) during 18 months with a follow-up period of 6 months. Based on our suicidal behavior monitoring pilot data (see above), we have calculated power in multivariate logit regression models, assuming a type I error of 0.05 and two-sided comparison. Using the effect sizes and standard deviations from our pilot data we expect our sample 1000 attempters and 100 reattempters during the follow-up) to provide 80% power to detect significant changes in death desire, suicidal ideation or suicide attempt related with sleep and appetite.

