### Data analysis

We will carry out descriptive analyses of all data collected separately by site and treatment. We will calculate means, variances and empirical quartiles, and assess the distribution and skewness of the data. If groups differ significantly on covariates then these scores will additionally be included as covariates in multivariate regression models.

We will use 3 multi-level logit regression to account for multiple observations per individual, to identify individual-level (sleep, appetite, socio-demographic, clinical data, treatment data) and site-level characteristics associated with death desire, suicidal ideation or suicide attempt. We will use hazards models to relate covariate characteristics (sleep, appetite, socio-demographic, clinical data, treatment data) with time to suicide re-attempt during the follow-up period**.** Data mining (machine learning) techniques will be used to examine risk factors, patterns of illness evolution and outcomes, and patient stratification by level of risk.

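### The suicidal event is not tied to the inclusion C-SSRS and no rule requires adjustment for entry ideation, so ideation already present at entry can enter the ideation and death-desire results

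*Protocol article*

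**What the plan says.** All references are to the protocol article.

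- **Primary outcome.** "The primary outcomes are suicidal events assessed by Columbia-Suicide Severity Rating Scale (C-SSRS) in control and intervention group during the 6-month follow-up period". No C-SSRS item, threshold, onset or worsening is given.
- **Objectives.** The principal objective correlates sleep quality with "suicidal events including and suicide attempts in a cohort of suicidal patients". A word appears to be missing, so the text does not settle whether ideation belongs to the event.
- **Intervention and control.** Patients "having attempted suicide in the current year, will be assigned to the intervention group". For the other arm: "Patient with no history of suicide behavior will be assigned to the control group". The apps that yield EMA and sensor sleep data go to the intervention group only.
- **Outcomes measures.** "The assessment of suicidal behaviors will include at the inclusion and completion of follow-up"; the C-SSRS heads the list that follows. An entry value therefore exists, but the Baseline assessment section does not list it.
- **Suicide and sleep monitoring.** The principal objective is evaluated by interviews and "EMA self-questionnaires including wish to live, wish to die, suicidal ideation, and suicide attempt during the follow-up period".
- **Sample size.** The sample is expected "to provide 80% power to detect significant changes in death desire, suicidal ideation or suicide attempt related with sleep and appetite".
- **Data analysis.** Multi-level logit models seek individual-level and "site-level characteristics associated with death desire, suicidal ideation or suicide attempt". A hazards model covers time to re-attempt. Clinical data are among the covariates, but inclusion C-SSRS is not named. The only explicit entry rule is to add covariates on which the groups differ significantly.

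**The concern.** The Background hypothesis is prospective: changes in sleep and appetite may come before a rise in suicidal behaviour. The Sample size section likewise speaks of changes. The logit models, as described, relate sleep to the presence of death desire, ideation or attempt, with no reference to the patient's state at inclusion.

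App-based sleep data exist only in patients with an attempt in the current year, some of whom may be ideating when they enter. The article itself describes poor sleep as a marker of depression, related in both directions. If entry ideators also sleep worse, their continuing ideation will link poor sleep to follow-up ideation even when sleep has no bearing on what happens next. The reader would then take a between-patient difference present on day 0 for a prospective signal.

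The stated covariate rule does not protect against this. It tests differences between intervention and control, whereas the confounding arises within the app group.

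**Working it through.** **1. The plan's own figure.** The stated 80% power cannot be reproduced, because the pilot effect sizes and standard deviations are not given. It can be turned round. With N = 1000, 100 events (rate 0.10) and two-sided alpha 0.05, the logistic formula for a continuous covariate gives

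ln OR per SD = (1.960 + 0.842) / √(1000 × 0.10 × 0.90) = 2.802 / 9.487 = 0.295, so OR = 1.34 per SD.

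If other covariates explain 10% or 30% of the variance in sleep, this becomes 1.37 or 1.42. The figure is used below only as a yardstick.

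**2. Which analyses are exposed.** The expected event count and the hazards model concern re-attempts, which are new events by nature. The logit models for death desire and ideation concern states that can persist from entry.

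**3. Share of events carried over.** The documents give no entry prevalence or persistence, so all rates here are assumptions. Let π be the proportion ideating at entry, q the proportion of those still ideating in follow-up, and r the new onset in the others. If any follow-up ideation counts,

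carried-over share = πq / (πq + (1 − π)r).

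With r = 0.10, the lowest case is 0.03 / (0.03 + 0.09) = 25% (π 0.1, q 0.3). The highest is 0.30 / (0.30 + 0.05) = 86% (π 0.5, q 0.6).

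**4. Effect on the sleep test.** Simulation with N = 1000 and 400 runs per cell. Sleep is normal with SD 1, shifted by d in entry ideators, and has no effect on follow-up given entry state. The table gives the percentage of runs in which a logit of follow-up ideation on sleep rejects at 0.05.

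| π | q | Carried over | Unadjusted, d = 0 | Unadjusted, d = 0.2 | Unadjusted, d = 0.5 | Adjusted for entry ideation, d = 0.5 |
|---|---|---|---|---|---|---|
| 0.1 | 0.3 | 25% | 5.0 | 7.5 | 12.8 | 5.5 |
| 0.1 | 0.6 | 40% | 5.0 | 13.0 | 48.5 | 4.0 |
| 0.3 | 0.3 | 56% | 6.0 | 12.0 | 39.5 | 5.0 |
| 0.3 | 0.6 | 72% | 5.5 | 33.8 | 96.0 | 5.3 |
| 0.5 | 0.3 | 75% | 4.8 | 12.3 | 51.8 | 4.8 |
| 0.5 | 0.6 | 86% | 2.8 | 39.8 | 98.5 | 4.3 |

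The Monte Carlo error at 5% is √(0.05 × 0.95 / 400) = 1.1 points. At d = 0.5 the unadjusted OR runs from 1.09 to 1.31 per SD; the top of that range is close to the yardstick of 1.34. Over all 18 cells the adjusted model rejects in 2% to 7%. Restricting to patients without entry ideation gives 3% to 7%, no better than adjustment.

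**5. Stronger assumptions.** With N = 500, π of 0.3 to 0.7, q of 0.6 or 0.8, r = 0.15 and d of 0.3 or 0.5, the unadjusted model rejects in 24% to 95% and the adjusted model in 4% to 6%. Replacing entry ideation by a depression score 1 SD higher in entry ideators still left up to 84% rejection. A depression measure is therefore not a safe substitute.

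**6. Attempts only.** No event is carried over. At d = 0.5 the unadjusted model rejects in about 6% when attempt risk is the same whatever the entry ideation. It rejects in 12% to 15% when that risk is 15% against 8%. The latter is ordinary confounding and much milder; adjustment brings it to about 4% to 5%.

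**The case against.** The strongest reply is that silence is being read as a rule. A reader might infer that the plan counts unchanged ideation as a primary event. No section says so, and much of the text points to attempts: the only event legible in the principal objective, the expected event count and the hazards model. **This stands.** What can be said is that carry-over is not excluded from the ideation and death-desire analyses.

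A reader might also infer that patients are enrolled because they are ideating. They are not: app patients are selected on an attempt in the current year, and controls have no suicidal behaviour. **This stands too**, and the rate of ideation at entry is unknown.

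Thirdly, the principal objective is worded as a correlation, with the timeline a secondary objective. If ideators sleep badly, that is a real association and not in itself a type I error. **This stands in part.** The rejection rates above are false positives only for the prospective question, but that is the question the Background poses.

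Fourthly, clinical data may already cover inclusion C-SSRS, and the full protocol or analysis plan may define the event. Neither can be ruled out. Still, the one explicit entry rule in the article is the between-group test, which looks in the wrong place.

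Finally, the simulation uses one observation per patient, whereas the plan is multi-level. That limits the figures as forecasts. It does not remove the mechanism, because a random intercept alone does not eliminate between-patient confounding by entry state.

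**Conclusion.** The point holds as a conditional risk in the ideation and death-desire logit models. The event is not defined against inclusion, an inclusion value is collected, and nothing in the article ensures that it is used.

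The size depends on three things: ideation counts in these analyses, sleep is related to ideation at entry, and entry ideation is left unadjusted. When the second fails, rejection stays at about 5%. When all three hold, it ranged in the N = 1000 simulations from 7.5% to 40% at a 0.2 SD shift and from 13% to 98.5% at 0.5 SD. Every rate behind these figures is assumed.

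The documents do not support the conclusion that the primary sleep association is spurious. Analyses of attempts and of time to re-attempt are free of carry-over.

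**What to change.** **Data analysis section.** Always enter the inclusion C-SSRS ideation level as a covariate in the logit models, whatever the group-difference test shows. Enter it in the hazards model as well, where it serves precision and covers any dependence of attempt risk on entry ideation. Use the inclusion assessment only as baseline, never as one of the repeated outcome observations.

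**Primary outcome section.** State that attempts during follow-up count as events. As a sensitivity analysis, report ideation that is new or worse than at inclusion separately from ideation that merely continues. Making new or worse ideation the primary definition is not needed: adjustment alone restores about 5% rejection, and under that definition a patient at the top ideation level at entry could never have an ideation event.

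**Cost.** Wording only, since the inclusion C-SSRS is already collected. The adjusted ideation association may be smaller and less favourable than the unadjusted one.
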